### **Protocol violation**

Any participant found to have entered this study in violation of the protocol will be discontinued from the study at the discretion of the Qualified Investigator. This will include any participant found to have been inappropriately enrolled (did not meet eligibility criteria). Participant non-compliance includes not showing up for study visits, not taking the investigational product as directed, or refusing to undergo study visit procedures. Participants who are found to be taking prohibited medications or supplements without the knowledge of the Qualified Investigator will also be withdrawn. Any major protocol deviations (i.e., those that increase the risk to participants and/or compromise the integrity of the study or its results) will result in participant discontinuation.

## **5 INVESTIGATIONAL PRODUCT**

### **5.1 Manufacturing and Storage**

The investigational product will be provided to KGK by the Sponsor. The investigational product will be carefully stored at the study site in a lockable, limited access area, accessible only to study team personnel in compliance with pertinent regulations. Only authorized persons will have access to the investigational product. The products will be stored at room temperature and will not be exposed to direct sunlight or heat. The investigational products will be kept in a locked investigational product storage room at KGK Synergize Inc. on receipt. An accountability log will be kept for the investigational products.

All unused investigational product will be returned to the study sponsor by KGK (at the sponsor's expense) or destroyed on receipt of written confirmation from the sponsor at study closeout (within one month of last subject visit).

Manufactured by:

W.R. Grace & Co. [name]

### **5.2 Labeling and Coding**

The investigational product will be labeled according to the requirements of ICH-GCP guidelines and applicable local regulatory guidelines. Investigational product will be randomized and coded by an unblinded person at KGK who is not involved in data collection or analysis.

### **5.3 Investigational Products**

| Dietary Ingredient                | Quantity (Qty)       |
|------------------------------------------|-----------------------------|
| Niagen™ (nicotinamide riboside chloride) | 100mg (1 capsule @ 100 mg)  |
| Niagen™ (nicotinamide riboside chloride) | 300mg (3 capsules @ 100 mg) |

Protocol 15NRHC: A randomized, double-blind, placebo controlled parallel study investigating the effects of Niagen™ (Nicotinamide Riboside) on Niagen™ metabolites in healthy adults

|                                          |                              |
|------------------------------------------|------------------------------|
| Niagen™ (nicotinamide riboside chloride) | 1000mg (4 capsules @ 250 mg) |
|------------------------------------------|------------------------------|

Non-medicinal ingredients: microcrystalline cellulose, veggie capsule

#### **5.4 Placebo:**

microcrystalline cellulose, veggie capsule

#### **5.5 Directions**

Participants will consume 4 capsules at the clinic (Day 0) after acquiring biological samples (blood, urine and muscle) and evaluating REE. Participants will be instructed to take 4 capsules daily after breakfast beginning the day after randomization visit (Day 1). The 4 capsules amount to a single dose of either placebo (a total of 4 placebo capsules) or 100mg NR (1 capsule containing 100 mg Niagen™ and three placebo capsules), 300mg NR (3 capsules containing 100 mg Niagen™ and 1 capsule containing placebo) or 1000mg (4 capsules containing 250 mg Niagen™). These capsules will be supplied in blister packs (4 per pack), whereby participants will open one blister pack daily to obtain the correct dose. If a dose is missed the participant should take the missed dose as soon as remembered. Participants are not to take more than 4 capsules per day. Clinic staff will also be instruct the participants to save all unused and open packages and return them to KGK at each visit for a determination of compliance.

#### **5.6 Randomization**

A randomization schedule will be created and provided to the Investigator indicating the order of randomization. Each participant will be assigned a randomization code according to the order of the randomization list generated using [www.randomization.com](http://www.randomization.com). Enrolled participants will be block randomized to the different treatment arms at Day 0.

#### **5.7 Unblinding and Allocation Concealment**

Unblinding should not occur except in the case of emergency situations. In the event that a serious adverse event occurs, for which the identity of the investigational product administered is necessary to manage the participant's condition, the treatment received by the subject will be unblinded and the investigational product identified. Concealment of the allocation of treatment will be employed through the use of opaque sealed envelopes, each labeled with a randomization number. Each envelope will contain information regarding the treatment associated with each randomization number. These envelopes will be readily available for the investigator to open in the event that it becomes necessary to know which product a participant is taking for the sake of their health care. The sponsor must be notified of any unblinding within 24 hours. Details of participants who are unblinded during the study will be included in the Final Report.

### **6 STUDY ASSESSMENTS**

See Appendix 1 for the schedule of assessments and procedures.

Protocol 15NRHC: A randomized, double-blind, placebo controlled parallel study investigating the effects of Niagen™ (Nicotinamide Riboside) on Niagen™ metabolites in healthy adults

### **6.1 Visit 1 - Screening (Day -28 to Day -16)**

At screening, a Subject Informed Consent Form will be given to the potential subject. The subject will read the information carefully and will be given the opportunity to seek more information if needed. The subject will also be provided with the option of taking the consent form home to review prior to making his or her decision. If agreeable, the subject will sign the consent form and receive a duplicate. Once consent has been obtained, the screening visit will proceed. After the subject has signed the informed consent, the screening number will be assigned sequentially and entered in the Screening and Enrollment Log. Screening numbers will be allocated in the chronological order of the subject's signing the informed consent.

Visit 1 includes:

- Review inclusion and exclusion criteria
- Review of medical history and concomitant therapies and current health status
- Seated resting blood pressure, and heart rate
- Weight and height measured and BMI calculated
- Collect blood samples for CBC, electrolytes (Na, K, Cl), HbA1c, creatinine, AST, ALT, GGT, BUN and bilirubin
- Urine pregnancy test for all female participants

Subjects will be asked to maintain current physical activity levels and record physical activity in a diary (dispensed at visit 2)

Subjects will be educated on the dietary restrictions required for the study by a dietician. These restrictions include:

1. Avoid foods containing high amounts of tryptophan and niacin
2. Limiting exposure to food containing moderate amounts of tryptophan and niacin (refer to appendix 2);
3. Avoiding foods and beverages known to contain NR during specified periods of time prior to and during the study. A list of these foods and beverages are provided below:
  - Food containing niacin (during the study)
  - Vitamins and health supplements containing niacin (nicotinic acid) or nicotinamide for 14 days prior to enrolment and during the study
  - Nutritional yeast (14 days prior to enrolment, during the study)
  - Whey proteins (14 days prior to enrolment, during the study)
  - Energy drinks (14 days prior to enrolment, during the study)

See Appendix 2 for a detailed list of food to avoid/limit

Study staff will be in contact with the subject weekly to facilitate dietary compliance once the dietary restrictions have begun.

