##### **4.1 Inclusion Criteria**

1. Healthy Male or female 40-60 years of age
2. BMI 25-30 kg/m^2
3. If female, subject is not of child bearing potential, which is defined as females who have had a hysterectomy or oophorectomy, bilateral tubal ligation or are post-menopausal (natural or surgically with > 1 year since last menstruation)

OR

Females of childbearing potential must agree to use a medically approved method of birth control and have a negative urine pregnancy test result. Acceptable methods of birth control include:

- Hormonal contraceptives including oral contraceptives, hormone birth control patch (Ortho Evra), vaginal contraceptive ring (NuvaRing), injectable contraceptives (Depo-Provera, Lunelle), or hormone implant (Norplant System)
  - Double-barrier method
  - Non-hormonal intrauterine devices
  - Vasectomy of partner
4. Healthy as determined by laboratory results, medical history, and physical exam
  5. Agrees to comply with study procedures
  6. Agrees to maintain current level of physical activity throughout the study and avoid exercising on the day of study visits 3 to 7 (prior to the visit).
  7. Agrees to refrain from consuming caffeine (i.e. coffee) on the days of study visits 3 to 7 (prior to the visit)
  8. Agrees to avoid taking Vitamin B3 (niacin, nicotinic acid, niacinamide) supplements or multivitamins 14 days prior to randomization and for the duration of the study period
  9. Has given voluntary, written, informed consent to participate in the study
  10. Agrees to avoid foods that contain high amounts of tryptophan and niacin and limit their ingestion of foods containing moderate amounts of tryptophan and niacin.

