##### **4.2 Exclusion Criteria**

1. Women who are pregnant, breastfeeding, or planning to become pregnant during the course of the trial.
2. Alcohol use >2 standard alcoholic drinks per day
3. History of alcohol or drug abuse within the past year
4. Medicinal use of marijuana
5. Diabetes (Type I or Type II)
6. Active peptic ulcer disease
7. Subjects taking lipid lowering drugs and blood pressure medications
8. History of renal and/or liver disease
9. History of pellagra or niacin deficiency

Protocol 15NRHC: A randomized, double-blind, placebo controlled parallel study investigating the effects of Niagen™ (Nicotinamide Riboside) on Niagen™ metabolites in healthy adults

10. Significant or untreated medical disorders including recent myocardial ischemia or infarction, unstable angina, uncontrolled hypertension, AIDS, malignancy, and neurological disorders including epilepsy, and recent cerebrovascular disease
11. Subjects with or who had recently experienced a traumatic injury, inflammation, infections or had undergone surgery.
12. Use of natural health products containing NR within 14 days prior to randomization and during the course of the study
13. Unstable medical conditions as determined by the Qualified Investigator
14. Clinically significant abnormal lab results at screening (e.g. AST and/or ALT > 2 x ULN, and/or bilirubin > 2 x ULN) will be assessed by the Medical Investigator
15. History of or current diagnosis of any cancer (except for successfully treated basal cell carcinoma) diagnosed less than 5 years prior to screening. Subjects with cancer in full remission more than 5 years after diagnosis are acceptable
16. Participation in a clinical research trial within 30 days prior to randomization
17. Allergy or sensitivity to study supplement ingredients
18. Allergy or sensitivity to lidocaine
19. Bleeding disorder
20. Serum creatinine  $\geq 130\mu\text{mol/L}$  for males and  $\geq 125\mu\text{mol/L}$  for females
21. Individuals who are cognitively impaired and/or who are unable to give informed consent.
22. Any other condition which in the Investigator's opinion may adversely affect the subject's ability to complete the study or which may pose significant risk to the subjects

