##### **Clinical reasons**

Protocol 15NRHC: A randomized, double-blind, placebo controlled parallel study investigating the effects of Niagen™ (Nicotinamide Riboside) on Niagen™ metabolites in healthy adults

A participant may be withdrawn from the study if, in the opinion of the Qualified Investigator, it is not in the participant's best interest to continue. Any participant who experiences a serious adverse event (SAE) may be withdrawn from the trial at the discretion of the Qualified Investigator. A participant will also be withdrawn due to adverse events causing clinically significant illness or the need for prohibited medication(s) during the trial. Any female subject who becomes pregnant during the course of the trial will be withdrawn.

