### 6.3 Visit 3 – Baseline (Day 0)

Eligible participants will return to the clinic in the morning, after fasting for 12 hours (nothing to eat or drink except water) for baseline assessments. Participants must not have consumed caffeine or exercised on the day of the visit, prior to the visit.

1. Review of medical history and concomitant therapies and current health status
2. A physical exam will be conducted
3. Participants will be randomized into the study.
4. Participants will be weighed and BMI will be calculated
5. Resting blood pressure and heart rate will be measured
6. REE will be evaluated
7. Study diaries and 3-Day Food Records will be collected and reviewed. Subjects will receive dietary counselling from a dietician.
8. Collect pre-dose urine sample for the measurement of Niagen™ metabolites and random urine creatinine analysis
9. Collect pre-dose blood for measurement of Niagen™ metabolite
10. Collect pre-dose blood samples for lipid panel, amino acid panel, hsCRP, AST, ALT, GGT and BUN
11. Collect muscle biopsy from the *Vastus Lateralis* of subject's leg for Niagen™ metabolite analyses.
12. New study diaries and 3-Day Food records will be dispensed to the participant. 3-Day Food records will be completed every week until the next visit, and the study diary will be completed daily.
13. Investigational product will be dispensed according to the randomization schedule.
14. After all assessments are completed the participant will take the first dose (4 capsules) of the product at the clinic.
15. Participants will be instructed in detail by site personnel about the treatment regimen.
16. The next visit will be scheduled for Day 7 this visit ( $\pm$  3 days).

Protocol 15NRHC: A randomized, double-blind, placebo controlled parallel study investigating the effects of Niagen™ (Nicotinamide Riboside) on Niagen™ metabolites in healthy adults

Study staff will be in contact with the subject weekly to facilitate dietary compliance.

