## 12 APPENDICES

### 12.1 Appendix 1 Schedule of Assessments

| Procedures/assessments                                                                                                                                          | Visit 1
Screening
Day -28 | Visit 2
Stabilization
Initiation
Day -14 | Visit 3
Baseline
Day 0 | Visit 4
Week 1
Day 7 | Visit 5
Week 2
Day 14 | Visit 6
Week 4
Day 28 | Visit 7
Week 8
Day 56 |
|-----------------------------------------------------------------------------------------------------------------------------------------------------------------|---------------------------------|---------------------------------------------------|------------------------------|----------------------------|-----------------------------|-----------------------------|-----------------------------|
| Informed consent                                                                                                                                                | X                               |                                                   |                              |                            |                             |                             |                             |
| Review inclusion/exclusion criteria                                                                                                                             | X                               |                                                   |                              |                            |                             |                             |                             |
| Review medical history and current health status                                                                                                                | X                               | X                                                 | X                            | X                          | X                           | X                           | X                           |
| Receive diet restrictions                                                                                                                                       |                                 | X                                                 |                              |                            |                             |                             |                             |

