| Urine pregnancy test                                                                                                                                            | X                               |                                                   |                              |                            |                             |                             |                             |
| Review concomitant therapies                                                                                                                                    | X                               | X                                                 | X                            | X                          | X                           | X                           | X                           |
| Randomization                                                                                                                                                   |                                 |                                                   | X                            |                            |                             |                             |                             |
| Height*, weight, heart rate, blood pressure
*Height will only be measured at Visit 1                                                                  | X                               |                                                   | X                            | X                          | X                           | X                           | X                           |
| Physical examination                                                                                                                                            |                                 |                                                   | X                            |                            |                             |                             |                             |
| Laboratory test:
CBC*, electrolytes* (Na, K, Cl),
HbA1c*, creatinine*, BUN,
AST, ALT, GGT, and bilirubin*
*Only measured at Visit 1, 6 and 7 | X                               |                                                   | X                            | X                          | X                           | X                           | X                           |

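### The only pregnancy test falls 16 to 28 days before the first dose, so no test verifies Exclusion 1 on Day 0; Inclusion 3 also leaves oophorectomy unqualified

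*Protocol*

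**What the plan says.** Exclusion 1 (Protocol section 4.2) bars "Women who are pregnant, breastfeeding, or planning to become pregnant during the course of the trial". Inclusion 3 (section 4.1) divides women into two classes. Those not of childbearing potential are defined as "females who have had a hysterectomy or oophorectomy, bilateral tubal ligation or are post-menopausal". All others must agree to an approved method of birth control and have a negative urine pregnancy test; no date is attached to either condition.

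The test itself appears in section 6.1 (Visit 1, Day -28 to Day -16) as "Urine pregnancy test for all female participants". In Appendix 1 the row "Urine pregnancy test" has one mark, under Visit 1, and the row "Review inclusion/exclusion criteria" likewise has one mark, under Visit 1. The lists for Visits 2 to 7 (sections 6.2 to 6.6) contain no pregnancy test.

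On Day 0 (section 6.3) the listed order is history and health-status review (item 1), physical exam (2), randomization (3), diary review (7), urine collection (8), muscle biopsy (11) and first dose (14). Item 8 reads "Collect pre-dose urine sample for the measurement of Niagen™ metabolites and random urine creatinine analysis".

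Under section 4.4, Clinical reasons: "Any female subject who becomes pregnant during the course of the trial will be withdrawn".

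**The concern.** An eligibility criterion that can change with time should be checked close to the point where it matters. Pregnancy status can change between Visit 1 and Day 0, and a urine test done very early in a pregnancy can be negative. The protocol ties several other criteria to randomization by a stated number of days (14 days in Inclusion 8 and Exclusion 12, 30 days in Exclusion 16), but gives the pregnancy test no such link.

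What is at stake is participant protection, not the primary analysis. Dosing lasts 8 weeks at up to 1000 mg a day. The Introduction says there are no published human reports on safety. It also reports that the sponsor's unpublished crossover study found the product well tolerated with no toxicity, but only at acute time-points of 1 to 24 hours. Neither statement bears on exposure in pregnancy. Having chosen to exclude pregnant women, the protocol should be able to show that the exclusion held when dosing started.

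**Working it through.** The protocol states no figure for this interval, so there is none to reproduce. The check is day arithmetic plus a comparison of sections.

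**Test to first dose** (sections 6.1 and 6.3)
- Longest: 0 - (-28) = 28 days. The Appendix 1 column head for Visit 1 gives Day -28 only, which is this case.
- Shortest: 0 - (-16) = 16 days.

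**Test to end of dosing** (section 6.6, Day 56 ± 3)
- At the nominal day: 56 + 16 = 72 to 56 + 28 = 84 days.
- With the visit window: 53 + 16 = 69 to 59 + 28 = 87 days. No repeat test falls in this period.

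**What could verify Exclusion 1 on Day 0**

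| Check | Scheduled on Day 0? | A pregnancy test? |
|---|---|---|
| Urine pregnancy test | No, Visit 1 only | Yes |
| Inclusion/exclusion review | No, Visit 1 only (Appendix 1) | No |
| History and health-status review | Yes, item 1 | No |
| Physical exam | Yes, item 2 | No |
| Diary review | Yes, item 7, listed after randomization | No |

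**Withdrawal rule.** Section 4.4 requires withdrawal on pregnancy. Sections 6.4 to 6.6 schedule nothing that would detect one apart from history, health-status and adverse-event review and diaries, so the rule has no scheduled test behind it.

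**Oophorectomy.** In Inclusion 3 the word bilateral qualifies tubal ligation only. Read literally, removal of one ovary places a woman in the class not of childbearing potential, and the birth control condition applies only to the other class. Section 6.1 tests every female participant, so the Visit 1 test still covers her.

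**Rough size per woman.** The protocol gives neither the number of women of childbearing potential nor a conception rate. Assuming 1% to 10% conceptions per year on contraception, the chance of conceiving in the gap is:
- low: 0.01 × 16/365 = 0.0004
- high: 0.10 × 28/365 = 0.008

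That is about 0.04% to 0.8% per woman using contraception throughout the gap. It leaves out a pregnancy already present but undetectable at Visit 1, and women not using contraception.

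**The case against.** The strongest reply is that the protocol is consistent: section 6.1 and Appendix 1 agree on a single test, Inclusion 3 adds contraception, Exclusion 1 bars women planning a pregnancy, and section 4.4 deals with any pregnancy that occurs. That stands. This is a design choice that can be improved cheaply, not a contradiction, and the expected number of pregnancies is small.

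It can also be said that Day 0 is not unguarded. That stands too. A reader might infer that a woman who conceives after Visit 1 would pass every check in the protocol. The documents do not support this, because history, health status, physical exam and diaries are all reviewed and could bring a known pregnancy to light. They would not reliably find one the woman does not know about.

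A reader might also infer that birth control need not start until randomization. The text sets no start date, but nothing in it delays use to Day 0, and some of the listed methods are standing ones (implant, intrauterine device, partner's vasectomy). The start is unstated, and no more than that can be said.

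On oophorectomy, the authors may well have meant removal of both ovaries. The wording does not say so, and a screener applying it literally would exempt a woman with one ovary from contraception. It would not exempt her from the test.

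**Conclusion.** The point holds as a modest gap in eligibility and safety checking. The only scheduled pregnancy test precedes randomization and first dose by 16 to 28 days, and no test verifies Exclusion 1 when exposure begins or supports the withdrawal rule afterwards. The unqualified oophorectomy wording is a separate, smaller defect that affects the birth control requirement only.

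The size is best stated as the interval in days, which needs no assumption. The documents do not support a count of affected women or pregnancies.

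A reader might go further and infer a material loss of Day 56 primary data. The documents do not support that either. Section 4.4 provides end-of-treatment evaluations at withdrawal where possible, section 8.3 carries the last observation forward in the intent-to-treat analysis, and section 8.1 already allows for 20% attrition.

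**What to change.** Verify Exclusion 1 on Day 0 with the same urine pregnancy test, run on the pre-dose urine already collected. In section 6.3, move urine collection (item 8) ahead of randomization (item 3) so that the result is read first, and add the entry to the Visit 3 column of Appendix 1.

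This closes the gap before dosing only; Day 0 to Day 56 would still have no test. The sponsor and investigator should therefore reconcile sections 4.1, 4.2, 4.4, 6.1 and 6.3 and Appendix 1 on three matters: what oophorectomy means in Inclusion 3, when the birth control requirement starts, and how a pregnancy after Day 0 is to be detected. The clinical content of those answers is theirs to decide.

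The cost of the Day 0 change is one test strip per relevant woman, a short reordering of the Day 0 steps and one schedule entry. It needs no extra visit or sample.
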